# PROTOCOL SUMMARY

**Title:** The DHA (docosahexaenoic acid) Oxford Learning and Behaviour (DOLAB) Study.

**Type of Study:** The study has two stages: Stage One is an

observational study and will be followed by Stage Two, a randomised controlled trial.

**Population:** Up to 600 children aged 7 years to 9 years from mainstream schools who are currently underperforming in reading (lowest tertile on nationally standardized achievement tests) will be included in Stage One of the study. 360 of these children will go on to be included in Stage Two, the randomised controlled trial.

**Number of Sites:** Up to fifty schools in Oxfordshire (and Buckinghamshire and Berkshire if required).

**Intervention:** The active compound (DHA, 600mg per day) and placebo (matching in package, taste and appearance) will be administered in an oral supplement.

**Study Duration and process:**

In Stage One of the study the parents/guardians of up to 600 children who are underperforming in reading (according to national tests or school records will be invited to consent to their child participating in a short school-based session, involving brief assessments of reading and working memory, an optional pinprick blood sample, and ratings from their teachers and parents. 360 of these children, whose assessment scores at Stage One indicate that they may benefit from this intervention,will be invited to join Stage Two, a randomised controlled trial. Baseline measures will be collected after which children will be randomly allocated to Omega-3 (DHA) or placebo conditions and followed up after 16 weeks. Recruitment will be carried out over two years. A ten percent sub-group of children in both groups will be randomly allocated to objective sleep monitoring.

## Research Questions

**Stage Two (RCT)**

**Primary: Can supplementation with Omega 3 (DHA) improve child behaviour and learning in underperforming children aged 7-9 years?** Outcomes assessed will include reading performance, working memory and ADHD-type symptoms (inattention, hyperactivity, impulsivity) as rated by teachers and parents.

**Secondary:**

**Might any treatment effects on behaviour or cognition be mediated by changes in child sleep?** (measured subjectively in all participants and objectively in a subset)

**Stage One (Observational Study)**

**Secondary: Do children’s levels of DHA or related fatty acids (**assessed objectively via a pinprick blood sample**) predict their learning, behaviour or sleep?**

**Are any observed changes in behaviour or cognitive performance associated with changes in blood fatty acid status?**

**Do sleep measures (and any changes in these) relate to objective measures of blood fatty acid status?**

# BACKGROUND AND RATIONALE

## Omega-3 for child behaviour and learning

Mounting evidence from human clinical trials shows that an increased dietary intake of the highly unsaturated Omega 3 fatty acids found in seafood (EPA and DHA) may have significant benefits for various aspects of mood, behaviour and learning (Freeman *et al* 2006). In children, four small controlled treatment trials have shown benefits for behaviour and/or learning from supplementation with these Omega 3 ([name] and Puri 2002, Stevens *et al* 2003, [name] and [name] 2005, Sinn & Bryan 2006), while two others have not (Voigt *et al* 2001, Hirayama *et al* 2004).

These studies have varied in their methodologies with respect to outcomes, populations studied and formulations used (see [name] 2006), but the most consistently reported benefits have been improvements in attention and concentration and reductions in disruptive or antisocial behaviour. Highly significant improvements in both reading and spelling performance were also found in the one study that assessed these outcomes ([name] and [name] 2005).

Child behaviour and learning problems have become a major problem in the UK and other developed countries. Conditions like attention-deficit hyperactivity disorder (ADHD) and reading disabilities (dyslexia) now appear to affect at least one in five school-age children, but many more show similar difficulties in milder form.These conditions have substantial costs not only for those directly affected, but for society as a whole (Burd *et al* 2003), and their consequences are lifelong.

Drug treatments such as methylphenidate are increasingly used to treat child behaviour problems, but these have undesirable side-effects. They also show only limited benefits for the core behavioural symptoms and none at all for learning.(NIH, 1998) Confirmation that dietary supplementation with omega-3 can significantly improve children’s behaviour and/or boost their performance in literacy and related cognitive skills would therefore have very important implications for policy and practice.

## Study Populations

To date, trials with children have focused on particular subgroups with specific developmental disorders of behaviour and/or learning such as ADHD, dyslexia or developmental coordination disorder (DCD).

- **The key question that has not yet been addressed is whether benefits reported for child behaviour and learning from omega-3 supplementation may extend to the general school population.**

The Oxford-Durham study ([name] and [name] 2005) focused on children who met DSM-IV criteria for DCD, but the vast majority had never previously been formally diagnosed with this or any other behavioural or learning disorder. The positive results found suggest that supplementation with omega-3 may help many other underperforming children in mainstream schools.

Around 1/3 of the Oxford-Durham study sample were also found to meet standard criteria for dyslexia / specific reading difficulties, while 1/3 scored in the clinical range for ADHD-type symptoms. This was fully expected given the usual high comorbidity between these developmental conditions - and the study was specifically designed to include reading, spelling and ADHD-type symptoms as primary outcomes.

As noted above, behaviour and learning difficulties of these kinds affect at least 20% of the school population, although the boundaries with normal function are unclear, and in practice most children with these kinds of difficulties are never formally diagnosed.

- **This study will therefore involve children attending mainstream schools who are underperforming academically (according to standardized national attainment tests).**

**To date, published studies in this area have been too small or unrepresentative to detect significant differences in treatment response according to eit**her age or sex.

Behaviour and learning difficulties usually compound with age, so early intervention is always preferable, but our clinical and research experience indicates that 7-9 year olds are the age group most likely to show significant improvements in literacy skills following omega-3 supplementation (or other interventions). Standardised national assessments of performance in a range of key areas (including literacy) are carried out at ages 7, 11 and 14 on all UK children attending state schools,[[1]](#footnote-2) and results from these can be used to select children who are underperforming for their age. For these reasons, this study will involve children aged between 7 and 9 years.

Published trials in this area have included mainly boys, who are more likely than girls to show overt behavioural and/or learning difficulties. The male:female ratio was lowest in the Oxford-Durham study (at around 3:1), but many females in this study showed a very good response to supplementation, an impression supported by our clinical work and unpublished pilot data. This study will therefore focus simply on children who are underperforming for their age, although possible sex differences will be explored in the analyses.

## Outcome Measures

With respect to behaviour, clinical rating scales are rarely sensitive enough to detect treatment effects, and neither these nor various computer tests designed to assess attention or impulsivity have proved successful to date (Voigt *et al*, 2001; Stevens *et al* 2003; Hirayama*, et al.*, 2004). In this study, behaviour will be assessed by both teachers and parents, using well-validated questionnaire rating scales that are (a) psychometrically sound, (b) suitable for general population use and (c) likely to be sensitive to any treatment effects. The Conners’ Scales (Conners 1997) were originally developed to assess pharmacological treatments for child behaviour problems, and have shown benefits in three of the successful RCTs of omega-3 for child behaviour and learning ([name] & Puri, 2002; [name] & [name], 2005; Sinn & Bryan 2006)

With respect to cognitive function, simple, transparent measures are again likely to be the most useful. The Oxford-Durham study showed clear benefits from fatty acid treatment for literacy skills (reading and spelling), and also on a simple, widely used test of working memory. Age-standardised tests of reading performance and working memory will therefore be used as primary outcomes in this study.

## Why sleep might be a mediator

Our own clinical and research work (jointly and independently) has long suggested that many of the benefits for mood, behaviour and cognition reported following omega-3 supplementation may in fact be mediated by improvements in sleep. ADHD and related child behaviour and learning difficulties are commonly associated with sleep problems (independently of medication effects), and these can exacerbate symptoms such as impulsivity or emotional lability as well as impairing attention, working memory and other aspects of cognition.

Many fatty acid derivatives play key roles in sleep initiation and maintenance (Yehuda 1998). Preliminary evidence from animal studies also suggests that fatty acid supplementation may help to reduce some of the anxiogenic effects of REM sleep deprivation (Yehuda 2007), and controlled studies of the effects of omega-3 on sleep in humans are now clearly warranted.

This study will therefore include simple subjective measures of sleep on all participants, as well as objective measures (using actigraphy) in a subset of children. If DHA supplementation could be shown to improve sleep parameters alone, this would be an extremely important finding with applicability to many other conditions. The ability to determine whether sleep may help to mediate any changes in child behaviour and cognition, and to explore associations with biochemical measures of fatty acid status, will also add considerably to the value of this study.

## Objectives

The primary objective of this trial is to determine whether DHA (in a daily dose of 600 mg.) will improve the behaviour and learning of normal children aged 7-9 years in mainstream state schools who are underperforming according to nationally standardized tests (≤ 33rd centile in literacy skills) but who had no other significant learning difficulties according to their teachers.

Secondary objectives include determining (a) whether blood biochemical measures of fatty acid status are associated with behavioural and cognitive outcomes, and with sleep; and (b) whether DHA supplementation changes children’s sleep, and if so, whether this may mediate any changes in behaviour and learning.

# TRIAL DESIGN

## Design

Stage One is an observational study of up to 600 underperforming children aged 7-9 years from the general school population. 360 children, whose assessment scores at Stage One indicate that they may benefit from the study intervention, will enter a

randomised controlled trial of DHA vs placebo for 16 weeks (fixed dose, parallel group study).

## Primary Endpoint

1. To confirm or refute that supplementation with Omega-3 fatty acids (DHA, 600mg/day) for 16 weeks improves behaviour and learning in children aged 7 – 9 years from mainstream schools who are underperforming academically.

## Secondary Endpoints

1. To assess whether levels of DHA or related fatty acids (assessed objectively via a pinprick blood sample) predict their learning, behaviour or sleep.
2. To assess whether any changes in behaviour or cognitive performance are associated with changes in objective measures of blood fatty acid status.
3. To assess whether any treatment effects on behaviour or cognition are mediated by changes in child sleep (measured subjectively in all participants and objectively in a subset).
4. To explore associations between child sleep and blood fatty acid status (at each timepoint, and with respect to changes following treatment).

.

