# ASSESSMENTS AND PROCEDURES (1) - Overview

Recruitment will be carried out over two years. There will be two assessment points for children in Stage One of the study: screening and baseline. Children in Stage Two of the study will be assessed at three points: screening, baseline and post-intervention.

This section will outline the overall study schedule, the measures that will be administered at each of the assessment points (and by whom), how they will be performed and what will be done with these data.

The following section will provide further details of each of the assessments used.

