### Stage One (Observational study)

Secondary outcomes

- Do children’s levels of DHA or related fatty acids (assess objectively via a pinprick blood sample) predict their learning, behaviour or sleep?
- Are any changes in behaviour or cognitive performance associated with changes in blood fatty acid status?
- Do sleep measures (and any changes in these) relate to objective measures of blood fatty acid status?

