## Sample Size

At Stage One, our previous studies indicate that a sample of 600 participants will be needed to identify an adequate number of eligible participants* for the intervention study, for which power calculations have been carried out (see below). This number of Stage One participants will also provide sufficient variance on all secondary outcome measures to ensure valid correlational analyses between these.

*Recruits to Stage Two must show ‘room for improvement’ on the main primary outcome (i.e. scoring within the lowest tertile on age-standardised measures of reading).

Following the only previous randomized controlled study to assess reading ability, power calculations were performed to estimate likely group sizes ([name] & [name], 2005)). These indicated that with significance set at 5% and power at 90%, groups of 180 (i.e. a total n of 360) would be required, based on our standardized reading change. Other outcomes would have required smaller sample sizes.

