# PUBLICATIONS

It is anticipated that at least three strong academic papers will be forthcoming from this study: one on the primary outcomes (to address whether DHA improves child behaviour and learning); a second on the objective blood biochemical measures and their correlations with the outcome measures; and a third looking at the role of sleep in relation to DHA and its effects on behaviour and learning. The data generated should also provide material for further academic publications in addition to these major ones.

We will also produce briefer papers for the ‘trade press’ as well as website material for posting on the University of Oxford Centre for Evidence Based Intervention website, and any such materials will be available for Martek Biosciences Corporation to use as they see fit.

[name]

[name]

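### Associations between outcome change and blood fatty acid change are filed under Stage One, but can be estimated only in randomised Stage Two children, and no text says how treatment arm enters

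*Protocol*

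**What the plan says.** Under Secondary Endpoints, the Protocol sets out as endpoint 2 "To assess whether any changes in behaviour or cognitive performance are associated with changes in objective measures of blood fatty acid status", and as endpoint 4 "To explore associations between child sleep and blood fatty acid status (at each timepoint, and with respect to changes following treatment".

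The outcome list in Statistical Considerations puts these questions under the heading Stage One (Observational study), for example "Are any changes in behaviour or cognitive performance associated with changes in blood fatty acid status". The Research Questions part of the Protocol Summary files them the same way.

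On measurement, the Overview of assessments states: "There will be two assessment points for children in Stage One of the study: screening and baseline". The section on fingerprick blood measures gives a baseline sample to children in both stages and a second sample to Stage Two children only. The blood test is optional.

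On method, the Sample Size section says that the Stage One number gives enough variance on the secondary measures for correlational analyses to be valid. Publications plans a separate paper, "a second on the objective blood biochemical measures and their correlations with the outcome measures". The Analysis Plan covers intention-to-treat change scores, two groups defined by baseline reading level, and median imputation by arm. It gives no model for these associations and does not say whether arm is taken into account.

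**The concern.** The protocol presents as observational a question that only the randomised children can answer. Among them, change in blood DHA is expected to depend on allocation; the protocol itself uses the blood data to check compliance. An analyst who follows the observational label and the word correlation has no cue to condition on arm.

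Without arm, one coefficient combines two quantities. The first is the difference between arms, which is the primary question again. The second is the relation within arms, which is not randomised and can reflect adherence and absorption. With a separate biochemical paper planned, a pooled correlation could be read as independent support for an effect that it largely restates. It could also understate a within-arm relation that exists.

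The Sample Size assurance cannot extend to change scores either. It rests on up to 600 Stage One children, whereas at most 360 can have a change score, and fewer if some decline blood sampling.

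**Working it through.** **The plan's own figure.** The protocol states "groups of 180 (i.e. a total n of 360) would be required", "with significance set at 5% and power at 90" per cent, "based on our standardized reading change". It gives no difference or SD, so 180 per group cannot be reproduced forwards. Solved backwards with a two-sided test (assumed; sidedness is not stated):

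d = (1.960 + 1.282) × √(2/180) = 0.342 SD

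One-sided, d would be 0.308. This only supplies a plausible effect size. It belongs to reading, and using it for other outcomes is an assumption.

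**Inputs**
- n = 360 paired samples, the maximum; n = 180 as a lower case, because blood is optional and uptake is not given.
- Equal allocation, implied by equal group sizes.
- D, the arm difference in blood change in within-arm SDs: not in the protocol; taken as 1, 2 and 3.
- ρ, the within-arm correlation: not in the protocol; taken as 0 or 0.20.
- d, the treatment effect on outcome change in within-arm SDs: 0 or 0.342.

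**Formula.** For two equal arms pooled without an arm term:

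r = (ρ + dD/4) / √[(1 + D²/4)(1 + d²/4)]

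Probability of significance, by Fisher z at two-sided 5%: approximately Φ(|atanh r| × √(n − 3) − 1.960).

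**Worked at D = 2, n = 360**
- d = 0.342, ρ = 0: r = 0.171 / √(2 × 1.029) = 0.119. Then atanh r × √357 = 2.26, and Φ(2.26 − 1.96) = 62%.
- d = 0, ρ = 0.20: r = 0.20 / √2 = 0.141. Then 2.69 − 1.96 = 0.73, and Φ(0.73) = 77%.
- d = 0.342, ρ = 0.20: r = 0.371 / 1.435 = 0.258.

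**All settings, n = 360**

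| D | d = 0.342, ρ = 0: pooled r (significant) | d = 0, ρ = 0.20: pooled r (power) | d = 0.342, ρ = 0.20: pooled r |
|---|---|---|---|
| 1 | 0.075 (30%) | 0.179 (93%) | 0.252 |
| 2 | 0.119 (62%) | 0.141 (77%) | 0.258 |
| 3 | 0.140 (76%) | 0.111 (56%) | 0.249 |

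With arm in the model, the test rejects in 5% of trials when ρ = 0 and has 97% power when ρ = 0.20, whatever D is.

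**Simulation check** (4,000 trials per setting, n = 360, D = 2), significant pooled versus arm-adjusted: 62.6% against 4.8% for d = 0.342, ρ = 0; 77.2% against 96.7% for d = 0, ρ = 0.20. The formula is confirmed.

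**Fewer blood samples.** With 180 pairs and D = 2, the first setting falls from 62% to 36%. In the second, pooled power is 47% against 77% adjusted.

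**Imputation.** A missing blood value replaced by its arm's median carries between-arm information only, and would add to the mixing. The protocol does not say whether its imputation rule covers the blood data.

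**The case against.** The strongest reply is that nothing here prescribes an unadjusted analysis. The endpoints are objectives, the Analysis Plan gives no model for them, and how arm enters an exploratory association is commonly settled in the SAP, which is not at hand. The sentence on correlational analyses concerns the Stage One number, so it most naturally means baseline correlations, where no arm exists. The publication list would fit partial or within-arm correlations equally well.

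Much of this stands. A reader might infer that the protocol commits to pooling the arms; no passage says so. A reader might also infer that a pooled correlation must either repeat the treatment effect or hide a dose-response. That is too strong. With both effects present the relation is inflated; with neither there is no distortion; at D = 1 the loss of power is only from 97% to 93%. Dose-response is not the protocol's term: the dose is fixed and the endpoint speaks of association. Nor is all of endpoint 4 affected, since its baseline part precedes treatment.

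What the reply does not answer is the filing. If the correlation sentence covers baseline only, the change questions have no stated framework at all, yet they are still listed under a stage in which change is not measured. That is an inconsistency in the protocol itself and not a detail left to the SAP.

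**Conclusion.** The concern holds in a limited form. It is certain from the text that the change and post-treatment associations are listed under Stage One and can be estimated only in randomised Stage Two children. It is conditional that the estimate will be distorted: this happens if the correlational framework is applied without arm.

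In that case the distortion could be material. A treatment effect alone would give a significant pooled correlation in about 30% to 76% of trials with 360 pairs (36% at D = 2 with 180 pairs). A within-arm correlation of 0.20 would appear as anything from 0.11 to 0.26, depending on D and on whether treatment works. These sizes rest on assumed values of D and ρ, on an effect size solved back from the reading sample size, and on the number of paired samples. The primary comparison is not touched.

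**What to change.** 1. Move the change and post-treatment association questions from Stage One to Stage Two, in both Research Questions and Outcome Measures.
2. Limit the Sample Size statement on correlational analyses to baseline associations.
3. State that the moved associations will be analysed with treatment arm in the model and baseline values as covariates, with the slope also shown by arm, in children with observed paired blood samples. Change scores may be kept; the arm term is what matters.
4. Label the results non-randomised associations, and state that they are not evidence additional to the randomised comparison.

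The cost is wording and one model per outcome. No new data, visits or participants are needed.

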# STUDY POPULATION

## Selection of participants

### Inclusion criteria

1. Children aged 7 – 9 years from mainstream state schools who are underperforming in literacy skills according to nationally standardized assessments of scholastic achievement at age 7 years (Key Stage 1[[2]](#footnote-3)).To be eligible, children must score ≤ 33rd centile for reading but be judged by their teachers to have no other significant learning difficulty.

**2**. English as a first language.

